##### Main outcome variables

In accordance with the aims of the study, the major outcome is tobacco cessation in patients with depression. The diagnosis of tobacco dependence will be made with the Spanish version of the MINI psychiatric interview substance dependence module adapted to tobacco [24]. This modification has been validated on a Spanish population with adequate psychometric properties [19]. Tobacco abstinence will be diagnosed by self-declared abstinence, self-administered Minnesota tobacco abstinence symptoms [25], expired air carbon monoxide [26], and cotinine in saliva. Tobacco abstinence, according to majoritarily-accepted criteria [27], has been defined using 2 concepts: 1. Occasional abstinence: In a follow-up visit, patients affirm that they have been abstinent, their levels of expired air carbon monoxide < 10 ppm, and cotinine levels in saliva < 5 ng/ml. Continuous abstinence: As of the visit at 30 days, patients affirm that they were abstinent the month before, expired air carbon monoxide levels < 10 ppm and cotinine levels in saliva < 5 ng/ml. Tobacco relapse will be diagnosed with the MINI psychiatric interview substance dependence module adapted to tobacco [24].

The diagnosis of depressive disorder will be made with the Spanish version of the MINI psychiatric interview, depression module [24], and the severity of the depression with the Spanish version of the Zung Self-Rating Depression Scale [22]. Recruitment will only include patients with depressive disorder and Zung scale scores < 60, which implies minimal to mild depression [22]. MINI psychiatric interview depression module [24], will be also used as criteria for depression relapse.

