### Measurements

The study personnel that carried out the measurements ([name]) will be unaware of which pharmacological treatment the patients is being administered ("blind"). The follow-up assessments will take place at baseline (clinical interview), D -1, D + 1, weeks 1, 2, 3, 4, 6, 8, 10 and 13, and months 4, 5, 6, 8, 10 and 12.

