#### Variables and instruments of measurement (See Table 1)

**Table 1 T1:** Study variables

**Instrument**	**Assessment area**	**Applied by**	**Time(s) of assessments**
Sampling form	Age, sex, inclusion/exclusion criteria	Family doctor	Baseline
Sociodemographic data form	Age, sex, marital status, educational level, Socio-economic group (28), occupation	Research assistant	Baseline
MINI psychiatric interview, depression and tobacco dependence modules (27)	Psychiatric diagnosis	Research psychiatrist	Baseline
Zung Self-Rating Depression Scale (22)	Severity of depression	Research assistant	Baseline and possible relapses
State of change (23)	State of change	Research assistant	Baseline
Self-declared abstinence	Tobacco abstinence	Research assistant	Baseline and all follow-up sessions*
Minnesota tobacco abstinence symptoms (24)	Tobacco abstinence	Research assistant	Baseline and all follow-up sessions*
Expired air carbon monoxide levels (25)	Tobacco abstinence	Research assistant	Baseline and all follow-up sessions*
Cotinine levels in saliva	Tobacco abstinence	Research assistant	Baseline and all follow-up sessions*
Fagerström test for Nicotine Dependence (29)	Tobacco dependence	Research assistant	Baseline and many follow-up sessions**
State-Trait Anxiety Inventory (STAI) (30)	Anxiety	Research assistant	Baseline and many follow-up sessions**
Plutchik Impulsivity Scale (31)	Impulsivity	Research assistant	Baseline and many follow-up sessions**
Visual analog scale	Efficacy self-perception	Research assistant	Baseline and many follow-up sessions**
Medical record	Pharmacological side-effect events	Research assistant	Baseline and many follow-up sessions**

*All follow-up sessions: D (cessation day) -1, D + 1, weeks 1, 2, 3, 4, 6, 8, 10 and 13, and months 4, 5, 6, 8, 10 and 12 (16 sessions in total) **Many follow-up sessions: weeks 1, 4, 8 and months 4, 6, 8, 10, 12.

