### Statistical methods

#### Sample size

To calculate the sample size we consider the tobacco cessation rate at 1 year follow-up as the main outcome variable. On the basis of published research data [5,6], we assume that this will be 35% in the control (NST) group, and we aim to detect a difference of 25% or more between any of the two groups (control and intervention). Published studies place placebo response at 10% [32]. Accepting an alpha risk of 0.05 and a beta risk of < 0.20 in a bilateral contrast, we would need 90 patients in each group [33].

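### The one-month recall in the continuous-abstinence definition does not span the two-month visit intervals after month 6, so about 3 of 12 months are not covered

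*Protocol article*

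**What the plan says.** All references are to the protocol article.

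- **Two abstinence concepts (Main outcome variables).** For occasional abstinence: "In a follow-up visit, patients affirm that they have been abstinent", with both biochemical limits met and no recall period given. For the other: "Continuous abstinence: As of the visit at 30 days, patients affirm that they were abstinent the month before", again with "expired air carbon monoxide levels < 10 ppm and cotinine levels in saliva < 5 ng/ml".
- **Schedule (Measurements; the same in Psychological intervention and under Table 1).** Baseline, then "D -1, D + 1, weeks 1, 2, 3, 4, 6, 8, 10 and 13, and months 4, 5, 6, 8, 10 and 12". Self-report, carbon monoxide and cotinine are taken at every follow-up session.
- **Relapse (Main outcome variables).** "Tobacco relapse will be diagnosed with the MINI psychiatric interview substance dependence module adapted to tobacco". Table 1 lists the MINI at baseline only, and no rule links a relapse diagnosis to loss of continuous abstinence.
- **Primary outcome.** Sample size states: "we consider the tobacco cessation rate at 1 year follow-up as the main outcome variable". Neither there nor in Analysis strategy is it said which of the two concepts this rate uses.
- **Nicotine products (Pharmacological intervention).** Treatment lasts 8 weeks. Controls receive nicotine patches, and patients in both arms may use nicotine gum or lozenges freely during that period.

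**The concern.** The recall period and the visit schedule are both fixed in the text, and they do not fit together. Once visits are two months apart, a question about the last month covers only half of each interval. The measure carries the name of continuous abstinence but can be met by someone who smoked between visits.

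This matters because the general aim is to show that topiramate is at least as effective as the standard treatment at 1 year. If missed episodes are spread evenly over both arms, the arms look more alike than they are. An aim of this kind is poorly protected against an error in that direction. The unasked months also cannot be recovered reliably afterwards.

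**Working it through.** **1. Schedule.** D−1 and D+1 (2), eight weekly-numbered visits (weeks 1, 2, 3, 4, 6, 8, 10, 13) and six monthly-numbered visits (months 4, 5, 6, 8, 10, 12) give 2 + 8 + 6 = 16. This reproduces the article's count of 16 sessions.

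**2. Time covered by the question.** Inputs: every visit from the 30-day visit (taken as week 4) to month 12, each looking back one month. Coverage is the union of the intervals [visit − 1 month, visit].

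| Visit (month) | Period asked about | Not asked since previous visit |
|---|---|---|
| 4 | 3–4 | under 1 day (week 13 falls at month 2.99) |
| 5 | 4–5 | none |
| 6 | 5–6 | none |
| 8 | 7–8 | 6–7 |
| 10 | 9–10 | 8–9 |
| 12 | 11–12 | 10–11 |

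With a month of 365.25/12 = 30.44 days, the uncovered time is 91.6 days, or 3.01 months. That is 25.1% of the year and 50% of months 6–12. Before month 6 coverage is essentially complete.

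**3. Sensitivity to the length of a month.**

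| Look-back | Uncovered days | Uncovered months | Share of year |
|---|---|---|---|
| 31 days | 89.6 | 2.9 | 24.5% |
| 30 days | 94.2 | 3.1 | 25.8% |
| 28 days | 106.2 | 3.5 | 29.1% |

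**4. Whether anything else stated closes the gap.** Carbon monoxide and cotinine are sampled at the visit and reflect recent smoking, so they cannot show an episode that ended a month earlier. The MINI is scheduled at baseline only and is not tied to this endpoint. The occasional definition gives no recall period, so it cannot be assumed to cover the whole interval.

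**5. Possible effect on the comparison.** Uncovered time is not a count of misclassified patients, and the article gives nothing from which to estimate one. As an illustration, let a fraction f of true failures be scored as abstinent, equally in both arms. The observed rate is p + f(1 − p), and the observed difference is (1 − f) times the true one. Take 35% for the control group and the 25-point difference from Sample size, placed here at 60%:

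| f (assumed) | Control | Topiramate | Difference |
|---|---|---|---|
| 0 | 35% | 60% | 25 points |
| 5% | 38.25% | 62% | 23.75 points |
| 10% | 41.5% | 64% | 22.5 points |
| 20% | 48% | 68% | 20 points |

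The factor (1 − f) is the same whichever arm does better.

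**6. After the change.** If the question covers the time since the previous visit (at most two months), uncovered time falls to 0.

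**The case against.** - **Most relapses would still be caught.** Smoking that runs into the month before the next visit fails the question or the biochemical limits. This stands: only an episode that starts and ends inside a gap month escapes. A reader might infer that any relapse in those months counts as success, and the text does not support that.
- **The forms may ask about the whole interval.** Self-report is taken at every session, and exact question wording is detail that an article commonly leaves to the full protocol. This is fair as a caution. But the article does state a recall period for this definition, and that period is one month.
- **The 1-year rate may simply be status at month 12.** This also stands. If the primary is occasional abstinence, the gaps affect only the continuous measure. If instead the continuous definition is applied at the month-12 visit alone, it is a one-month measure covering 1 of 12 months, and its name is still not earned.
- **The bias may not run towards similarity.** Cotinine comes from nicotine, so patients using patches, gum or lozenges can exceed 5 ng/ml while abstinent from tobacco. If visits are chained from week 4 with the cotinine limit at each, this lowers the continuous rate, mainly in the control arm. A reader might infer that the rate is overstated in both arms and the comparison pulled towards equality. The documents do not establish either.
- **Two definitions need not mean two tests.** A reader might infer an inflated false-positive risk. Nothing says that both will be tested as primary, and at month 12 the two are close to nested, so treating them as independent tests would be unsuitable.

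**Conclusion.** The concern holds in a limited form. As written, the continuous-abstinence rule leaves months 6–7, 8–9 and 10–11 unasked: about 3 of 12 months, or 2.9 to 3.5 depending on the length of a month. No other stated measurement or rule closes the gap. An episode confined to one of those months can be scored as continuous abstinence.

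This assumes that the recall period is applied literally and that visits from week 4 onward are chained. The extent of misclassification is unknown. The shrinkage in the table depends on an assumed f and on f being equal in the two arms, and the net direction of bias is not established. The effect reaches the primary result only if the 1-year cessation rate uses the continuous definition, which the article leaves open. It is a flaw in a stated definition that is cheap to correct, not a demonstrated bias in the main result.

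**What to change.** 1. **Main outcome variables:** at each visit ask about any smoking since the previous visit, in place of the month before.
2. **Same section:** define 12-month continuous abstinence as no smoking reported at any visit from week 4 to month 12, with carbon monoxide below 10 ppm at each of those visits. Apply the cotinine limit of 5 ng/ml only from week 10. That is the first visit after the 8 weeks of nicotine products, assuming treatment starts at about cessation day. If it starts later, the cotinine criterion should start correspondingly later. Requiring cotinine confirmation from week 4 would fail abstinent users of nicotine products, mainly controls.
3. **Sample size and Analysis strategy:** state which of the two definitions is the 1-year primary outcome, with the other as secondary.

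The cost is one changed question and a few sentences, with no added visits or assays. The downsides are two-month recall at the month 8, 10 and 12 visits, a slightly lower continuous rate, and no cotinine confirmation at weeks 4, 6 and 8. The change has to be in place before the question is first used.

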### Setting and study sample

Patients will be recruited from any of the 29 primary health care centres in the city of Zaragoza (Aragonese Health Service), Spain. Patients will be recruited by doctors working in these primary care centres until the required sample is completed, without a quota of patients assigned for every centre.

Patients considered for **inclusion **are those aged 18–65 years, able to understand and read Spanish, who fulfil criteria for major depression (DSM-IV criteria), with scores on the Zung Self-Rating Depression Scale < 60 [22] (implying minimal to mild depression), who smoke more than 20 cigarettes/day, fulfil preparation state of change according to Prochaska & DiClemente [23], voluntarily ask for a tobacco cessation therapy, and sign informed consent. Those **excluded **will be patients with active psychosis and/or treatment with antipsychotic drugs, alcohol or drug abuse, and pregnancy or lactation.

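### Depression relapse is defined by the same MINI diagnosis that patients need to enter, with no remission required, and the Zung scale that could show worsening is repeated only when a relapse is suspected

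*Protocol article*

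**What the plan says.** Under Setting and study sample, the protocol article admits patients "who fulfil criteria for major depression (DSM-IV criteria), with scores on the Zung Self-Rating Depression Scale < 60". Main outcome variables names the instrument for that diagnosis: "The diagnosis of depressive disorder will be made with the Spanish version of the MINI psychiatric interview, depression module [24". It gives severity to the Zung scale and repeats the entry limit: "Recruitment will only include patients with depressive disorder and Zung scale scores < 60, which implies minimal to mild depression". The paragraph closes with the relapse rule, under which the same MINI module "will be also used as criteria for depression relapse". No remission, symptom-free interval, new episode or change from baseline is attached to that rule.

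Table 1 gives the MINI row as "Psychiatric diagnosis Research psychiatrist Baseline", with no follow-up time. It lists the Zung at baseline and at possible relapses. The State-Trait Anxiety Inventory (STAI), the impulsivity scale and the self-efficacy scale are instead repeated at a fixed set of follow-up sessions. The Analysis strategy counts Zung severity among the process variables and plans linear mixed models for depression alongside anxiety, impulsivity and efficacy.

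**The concern.** Relapse means the return of a condition that had gone away. Here the entry condition and the relapse criterion are the same positive MINI, so an unbroken entry episode satisfies both. A count of relapses reported under this rule would mix patients who never remitted with patients who remitted and fell ill again, and would say nothing about patients who got worse.

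This matters because everyone in the trial has depression, one arm receives a psychoactive drug, and relapse is the only depression event that the article defines over the year. The Zung scale would be the natural way to see deterioration. Its repeat, however, depends on someone suspecting a relapse, so the planned model of depression severity would have follow-up values only for patients picked out by that suspicion. An analysis plan cannot repair this afterwards, because severity that was not measured at follow-up cannot be recovered.

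**Working it through.** No figure in the article bears on this point, so there is nothing to reproduce. The check sets the statements side by side and follows what they imply.

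**1. What the relapse label measures**

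- Input from Setting and study sample and Main outcome variables: all patients have the MINI diagnosis at entry, so the share positive at baseline is 1.
- Input from Main outcome variables: relapse is a positive MINI, with no other condition.
- Let r be the share no longer meeting the diagnosis at a follow-up MINI, and w the share whose depression truly worsened among those still meeting it.
- Share classed as relapse if all patients were tested = 1 − r. The quantity w does not appear.

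The article gives no remission rate. With r assumed at 20%, 40% or 60%:

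| Assumed remission r | Labelled relapse (1 − r) | With true worsening w of 0%, 10% or 30% |
|---|---|---|
| 20% | 80% | 80%, 80%, 80% |
| 40% | 60% | 60%, 60%, 60% |
| 60% | 40% | 40%, 40%, 40% |

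Read literally, the criterion measures non-remission. These rows illustrate the logic. They are not predictions, because Table 1 does not plan a follow-up MINI for all patients.

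**2. Whether the Zung fills the gap as scheduled**

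- Routine follow-up sessions for the STAI, from the footnote to Table 1: weeks 1, 4 and 8 (3), plus months 4, 6, 8, 10 and 12 (5). 3 + 5 = 8.
- Routine follow-up sessions for the Zung, from Table 1: 0. It is repeated only if a relapse is suspected.
- Routine follow-up sessions for the MINI, from Table 1: 0.

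**3. What this does to the planned mixed model**

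The Analysis strategy treats depression like anxiety, impulsivity and efficacy, each of which has eight routine follow-up values. For depression, a patient in whom no relapse is suspected contributes a baseline value only and carries no information on change. A patient with a later Zung has one because of something observed after randomisation. If the trigger is suspected depression, whether a value exists depends on the unseen current severity, and a mixed model does not correct for that. Table 1 does not say whether depression or tobacco relapse is meant. If tobacco relapse is meant, the subset is selected on the cessation outcome instead. On either reading, the arms would be compared within a group formed after randomisation.

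**The case against.** The strongest reply is that the article separates the roles: the MINI diagnoses, the Zung measures severity, and the Analysis strategy models severity. Worsening is therefore not left to the relapse label. That stands. A reader might infer that the trial as a whole cannot show whether either drug worsens depression, and the documents do not support this. The limit lies in the MINI criterion and in the Zung schedule, and regular Zung values would remove it.

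A second reply is that unchanged patients need never be counted as relapses, because no routine follow-up MINI is planned. That also stands. A reader might go on to estimate how many patients per arm would be mislabelled. Such a number needs both a persistence rate that the article does not give and follow-up testing of every patient that it does not schedule.

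Third, relapse of depression appears in neither the Objectives, the Secondary variables, the Sample size nor the Analysis strategy, so no planned comparison by arm is diluted. This is correct and limits the weight of the point. A comparison of MINI-positive proportions by arm, if all patients were tested, would even be a valid randomised comparison of persistence.

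Fourth, the ordinary sense of relapse implies remission, and a journal article may leave the operational rule to a fuller document. This answers only part of the point. The article states a criterion that overlaps with its own entry condition, and it states a Zung schedule that does not fit its own analysis. Both are written in the text and are more than omissions.

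Finally, the article never says that the entry episode must be current. If patients in remission were meant, the criterion could work for them. No section says so, and the Zung limit is glossed as minimal to mild depression, not as remission.

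**Conclusion.** The point holds in a limited form. On the plain reading, a patient whose entry episode persists meets the relapse criterion, and that label cannot register worsening. The instrument that could register it, the Zung, has no routine follow-up assessment against eight for the STAI, although the article plans to model both in the same way. Follow-up severity would therefore come from a selected subset.

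This rests on reading the entry diagnosis as a current one and on taking Table 1 as the full assessment schedule. No count of affected patients can be derived from the article. The one-year cessation comparison and its sample size are unaffected. The correction is worth making before recruitment because missing follow-up severity cannot be reconstructed later.

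**What to change.** - **Table 1:** schedule the Zung at the eight follow-up sessions already used for the STAI (weeks 1, 4 and 8; months 4, 6, 8, 10 and 12).
- **Analysis strategy:** compare change from baseline in the Zung by arm, for all randomised patients, in the linear mixed model already planned.
- **Main outcome variables:** call a positive MINI at follow-up *depression present*. Reserve *relapse* for a patient with a documented earlier MINI-negative assessment in the trial.
- **If patients in remission were intended:** reconcile the entry wording in Setting and study sample with that in Main outcome variables instead.

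The cost is wording plus a few minutes of self-rating at eight visits that already take place, given by the research assistant whom the article describes as blind to treatment. No cut-off on the Zung is needed, since change is analysed on the continuous scale. Routine MINIs at every visit are not needed either; Table 1 has the research psychiatrist do them, so they would take that person's time. The price is that relapse in the strict sense can be declared only where a negative follow-up MINI happens to be on record, so the Zung becomes the main source on the course of depression.

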##### Secondary variables

-The following socio-demographic data will be collected: sex, age, marital status (single, married/relationship, separated/divorced, and widowed), education (no studies, primary, lower secondary, upper secondary, university), occupation and social class (I, II, IIIN, IIIM, IV and V of the British Registrar General's Scale) [28].

-Tobacco dependence as measured by the Spanish version of the Fagerström test for Nicotine Dependence [29].

-Anxiety trait and state as measured by the Spanish version of the State-Trait Anxiety Inventory (STAI) [30].

-Impulsivity as measured by the Spanish version of the Plutchik Impulsivity Scale [31].

-Visual analogue scale for efficacy self-perception (range 0–10).

-Pharmacological side-effect events from the medical record.

### Statistical methods

#### Sample size

To calculate the sample size we consider the tobacco cessation rate at 1 year follow-up as the main outcome variable. On the basis of published research data [5,6], we assume that this will be 35% in the control (NST) group, and we aim to detect a difference of 25% or more between any of the two groups (control and intervention). Published studies place placebo response at 10% [32]. Accepting an alpha risk of 0.05 and a beta risk of < 0.20 in a bilateral contrast, we would need 90 patients in each group [33].

